### Blinding

During the course of this clinical trial, the assessor will not contact any participant at any point of time other than the time of assessment. Furthermore, unblinding will not be permitted. However, if serious adverse events (SAEs) occur, unblinding will be permitted after an agreement among the researchers. For prevention of bias with regard to selection, performance, and attrition caused by nonblinding of participants and practitioners, only individuals without conflicts of interest or preconceived positions will be involved in this study. All practitioners who will perform the interventions will receive training in clinical trials before participation.

### Interventions

Participants in the CCR group will receive RehaCom cognitive rehabilitation once (30 min) a day, 3 days per week (excluding Saturday and Sunday) for 8 weeks. Participants in the EA-CCR group will receive EA at Baihui (GV20), Sishencong (EX-HN1), Fengchi (GB20), and Shenting (GV24) in addition to RehaCom cognitive rehabilitation once (EA:30 min, CCR:30 min) a day, 3 days per week (excluding Saturday and Sunday) for 8 weeks. EA will be performed first, followed by CCR. The treatment will be administered by Korean medicine doctors with 6 years of formal university training in Korean medicine and a license to administer treatment. To ensure strict adherence to the study protocol, the doctors will receive training together and use the same techniques.

#### Electroacupuncture treatment

EA will be performed at the following acupoints: Baihui (GV20), Sishencong (EX-HN1), Fengchi (GB20), and Shenting (GV24, [10]). Only sterile, stainless steel, disposable acupuncture needles (size 0.25 × 30 mm, product no. A84010.02; Dong Bang Acupuncture, Inc., Boryeong, Republic of Korea) with guide tubes and an EA stimulator [CELLMAC PLUS (STN-330), product no. A16010.04; Stratek, Co., Ltd., Anyang, Republic of Korea] will be used. With the patient in a sitting position, the needles will be subgaleally inserted at an angle of 15–30° along the scalp. GB20 will be punctured 17–30 mm in the direction of the tip of the nose. GV24, the anterior EX-HN1, and GV20 will be punctured in the forward direction, while the left, right, and posterior EX-HN1 will be punctured in the direction of GV20. The depth of insertion will be 9–24 mm depending on the location of the needle [26]. After insertion, the needles will be left in position for 30 min. Manual stimulation will not be used. GV24 and GV20, the left and right EX-HN1, the anterior and posterior EX-HN1, and the left and right GB20 will be subjected to EA under the following parameters: continuous waves, frequency 3–15 Hz, and intensity 2–4 mA. Each participant will receive a total of 24 30-min sessions (three times per week for 8 weeks [10] see (Table 1).

**Table 1 Tab1:** Revised Standards for Reporting Interventions in Clinical Trials of Acupuncture (STRICTA)

	Item criteria	Description
1. Acupuncture rationale	1a) Style of acupuncture	Korean medicine therapy
	1b) Reasoning for treatment provided—based on historical context, literature sources, and/or consensus methods, with references where appropriate	1) Discussion among four doctors who practice Korean medicine (consensus) 2) Textbook of acupuncture and moxibustion medicine 3) Relevant articles [10] Selection of treatment regions based on textbooks, related papers, and expert discussions
	1c) Extent to which treatment varied	Standardized treatment
2. Details of needling	2a) Number of needle insertions per subject per session (mean and range where relevant)	8
	2b) Names (or location if no standard name) of points used (unilateral/bilateral)	Baihui (GV20), Sishencong (EX-HN1), Fengchi (GB20), and Shenting (GV24)
	2c) Depth of insertion, based on a specified unit of measurement or on a particular tissue level	After the needles are inserted into the acupoints subgaleally along the scalp at an angle of 15–30°, GB20 will be punctured 17 –30 mm in the direction toward nose tip. GV24, the anterior EX-HN1, and GV20 will be punctured forwards, and the left, right and posterior EX-HN1 toward GV20. The depth of insertion will be 9–24 mm depending on the location of the needle [26]
	2d) Responses sought	No de qi or muscle twitching; only sensation due to needle insertion
	2e) Needle stimulation	Electrical stimulation
	2f) Needle retention time	30-min per session
	2 g) Needle type	Sterile, stainless steel, disposable acupuncture needles (size 0.25 × 30 mm; Dong Bang Acupuncture, Inc., Boryeong, Republic of Korea; Product no. A84010.02)
3. Treatment regimen	3a) Number of treatment sessions	24
	3b) Frequency and duration of treatment sessions	Three times/week for 8 weeks, 30 min per session
4. Other treatment components	4a) Details of other interventions administered to the acupuncture group	RehaCom cognitive rehabilitation
	4b) Setting and context of treatment—including instructions to practitioners—as well as information and explanations given to patients	Practitioner-patient conversation about the context of the treatment, life habits, and daily life management
5. Practitioner background	5a) Description of participating acupuncturists	Korean medicine doctor with the following qualifications: 6 years of formal university training in Korean medicine, a license
6. Control or comparator interventions	6a) Rationale for the control or comparator in the context of the research question with sources that justify the choice	Zhang H, Zhao L, Yang S, Chen Z, Li Y, Peng X, Yang Y, Zhu M. Clinical observation on effect of scalp acupuncture for mild cognitive impairment [10]
	6b) Precise description of the control or comparator; details for items 1–3 above with the use of sham acupuncture or any other type of acupuncture-like control	Elctroacupuncture combined with computer-based cognitive rehabilitation group will receive the RehaCom cognitive rehabilitation after electroacupuncture treatment by same practitioner. The participants will be generally in seating position and will receive CCR using the RehaCom software. We will use 6 different therapeutic programs that seek to restore attention, memory, and executive functions. Each program has different tasks from which participants choose during each therapy session. The CCR will last 30 min each time, three times a week, for a total of 24 sessions

#### RehaCom cognitive rehabilitation

All participants will receive RehaCom cognitive rehabilitation in the sitting position. Six different therapeutic programs that seek to restore attention, memory, and executive functions will be used. Each program has one to four different tasks from which participants can choose during each therapy session. Each participant will receive a total of 24 30-min sessions (three times per week for 8 weeks).

During the clinical trial period, all participants will be allowed to use routine management regimens, existing medications (e.g., those for hypertension, diabetes, or hyperlipidemia), and medications for maintaining and improving their health status. However, they will not be permitted to engage in other treatments for ameliorating MCI symptoms. All medical devices, including the acupuncture needles, EA stimulator, and RehaCom software, will be inspected by the investigators, who will record the results of check-ups in the management register.

### Outcome measurements

Scores for the ADAS-K-cog, MoCA-K scale, CES-D, K-ADL scale, K-IADL scale, and EQ-5D-5 L will be recorded before treatment, at the end of treatment, and at 12 weeks after treatment completion.

#### Primary outcome

In accordance with the study objective, an improvement in cognitive function assessed using the ADAS-K-cog will be considered the primary outcome of the study. The ADAS-cog was developed by Rosen et al. [27] for the evaluation of comprehensive cognitive functions involving memory, language, praxis, and frontal lobe function. It was subsequently translated into Korean and validated [28]. This tool is sensitive to changes over time and includes subscales for testing list learning, object naming, commands, ideational apraxia, construction, orientation, and recognition. The possible total score is 70, with a higher score indicating a higher degree of deficit [29].

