### Hypothesis

The null hypothesis is that the improvement in cognitive function achieved with EA-CCR is not superior to that achieved with CCR in patients with MCI.

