### Study design

The study design is in accordance with the Standard Protocol Items: Recommendations for Interventional Trials (SPIRIT) and Consolidated Standards of Reporting Trials (CONSORT) 2010 guidelines [24, 25] (see Additional file 1). The study is a prospective, outcome assessor-blinded, parallel-arm, single-center (DongShin University Gwangju Korean Medicine Hospital, Republic of Korea), pilot randomized controlled clinical trial with a 1:1 allocation ratio. A total of 36 participants who meet the inclusion and exclusion criteria will be randomly allocated to an EA-CCR or a CCR (*n* = 18 each) group. Participants in the CCR group will receive RehaCom cognitive rehabilitation only, while those in the EA-CCR group will receive EA at Baihui (GV20), Sishencong (EX-HN1), Fengchi (GB20), and Shenting (GV24) along with RehaCom cognitive rehabilitation. The treatment duration will be 8 weeks in both groups. The primary outcome measure will be an improvement in cognitive function evaluated using the Korean version of the Alzheimer’s Disease Assessment Scale-cognitive subscale (ADAS-K-cog). The secondary outcome measures will include changes in scores for the Korean version of the Montreal Cognitive Assessment (MoCA-K) scale, Center for Epidemiological Studies-Depression Scale (CES-D), Korean Activities of Daily Living (K-ADL) scale, Korean Instrumental Activities of Daily Living (K-IADL) scale, and European Quality of Life Five Dimension Five Level Scale (EQ-5D-5 L). All scale scores will be recorded at baseline (before intervention), 8 weeks after the first intervention (i.e., at the end of the intervention), and 12 weeks after completion of the intervention.

This study protocol complies with the principles of the Declaration of Helsinki and Korean Good Clinical Practice guidelines and has been approved by the Ministry of Food and Drug Safety (Medical Device Clinical Trial Plan approval number 859). The trial has been registered at cris.nih.go.kr (registration number, KCT0003415). The study design is summarized in Figs. 1 and 2.

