### Statistical analysis

A statistician who is not involved in the clinical trial will analyze the final data. We will perform a per-protocol analysis (PP group) for the assessment of efficacy with a supplementary full analysis set (FA group). We will compare the results of analyses between the PP and FA groups and confirm whether there are statistically significant differences between the two groups. If there is a significant difference, the cause will be reviewed and reflected in the efficacy assessment. All statistical analyses will be performed using SPSS version 21 software (IBM Corp.).

Baseline characteristics will be described and compared. Continuous data will be presented as means and standard deviations and compared using the independent *t* test or Wilcoxon rank sum test, while categorical data will be presented as frequencies and percentages and compared using the chi-squared test or Fisher’s exact test.

Changes in scores for the ADAS-K-cog, MoCA-K scale, CES-D, K-ADL scale, K-IADL scale, and EQ-5D-5 L at 8 weeks (at the end of the intervention) and 20 weeks (12 weeks after the end of the intervention), relative to the baseline score, will be analyzed for each group using the paired *t* test or Wilcoxon signed rank test. The degree of changes at each time point will be evaluated using repeated measures analysis of variance and the two-sample *t* test or Wilcoxon rank sum test. Subanalyses will be applied to the statistical analysis according to the participant age. All reported *P* values will be two-sided with confidence intervals at the 95% levels. A *P*value of < 0.05 will be considered statistically significant.

Data for participants who meet the dropout criteria (i.e., < 75% compliance with the protocol procedures [received less than 18 of the 24 scheduled treatment sessions], incidence of SAEs, reluctance to continue the trial, incomplete data that could influence the trial, large error in protocol or significant deviation in implementation, or decision to terminate trial participation by the PI or IRB) will be excluded. Missing values will be implemented by the last observation carried forward method. Interim analyses will not be performed.

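### The ADAS-K-cog primary has no named time point or deciding test; if any planned between-group result may count, the false-positive chance is about 8-10%, not 5%

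*Protocol article*

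**What the plan says.** The Primary outcome section states that "an improvement in cognitive function assessed using the ADAS-K-cog will be considered the primary outcome of the study". The Study design section repeats this: "The primary outcome measure will be an improvement in cognitive function evaluated using the Korean version of the Alzheimer’s Disease Assessment Scale-cognitive subscale". Neither gives a visit, a summary measure or a contrast.

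The Hypothesis section is comparative but also has no time point: "The null hypothesis is that the improvement in cognitive function achieved with EA-CCR is not superior to that achieved with CCR".

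The Statistical analysis section treats ADAS-K-cog and the five secondary scales alike. Changes are taken "at 8 weeks (at the end of the intervention) and 20 weeks (12 weeks after the end of the intervention"), and within-arm change "will be analyzed for each group using the paired" t test or its rank counterpart. The comparison between arms is introduced by "The degree of changes at each time point will be evaluated using repeated measures analysis of variance and the two-sample", where the last-named comparison may be parametric or rank-based. All P "values will be two-sided with confidence intervals at the 95% levels", and a P "value of < 0.05 will be considered statistically significant". The section ranks neither visits nor tests, and it describes no adjustment for using more than one.

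**The concern.** A primary outcome needs a time point to be a defined quantity. Here the two post-baseline visits stand on an equal footing, and the analysis section sets up parallel between-group tests at the same threshold. The problem is therefore in what the text fixes, and goes beyond detail left to another document.

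Two things are at stake. First, if significance at either visit, or from either kind of test, can be presented as meeting the primary, the error rate for that claim exceeds 5%. Second, the plan gives no conclusion when results disagree: significant at week 8 but not at week 20, or by the two-sample test but not by the ANOVA. The choice would then be made after the results are known.

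**Working it through.** **Inputs from the article.** 18 participants per arm (Sample size estimation); two post-baseline visits, weeks 8 and 20; two-sided 0.05 per test; between-group comparison by repeated measures ANOVA and by two-sample tests (Statistical analysis). The article claims no familywise error rate and no power, so there is no stated figure to reproduce beyond the 0.05 threshold.

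**Assumptions.** No true effect, normal scores with equal variances, complete data, and a correlation *r* between visits of 0.3 to 0.85. The article gives no correlations.

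**Step 1: correlation of the two change scores.** Both changes subtract the same baseline, so they are correlated.
- Equal correlation *r* between all visits: covariance 1 − *r*, each variance 2(1 − *r*), so the correlation is 0.5 whatever *r* is.
- First-order autoregressive: the correlation is √(1 + *r*)/2, which is 0.57 at *r* = 0.3 and 0.68 at *r* = 0.85.

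The relevant range is therefore about 0.5 to 0.7.

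**Step 2: either visit significant, one test each (normal approximation).**
- If independent: 1 − 0.95² = 9.75%.
- In one direction: 0.025 + 0.025 − P(both Z > 1.96). At correlation 0.5 the joint term is 0.0046, giving 0.0454. At 0.68 it is 0.0078, giving 0.0422.
- In both directions, 1 − P(|Z₁| ≤ 1.96 and |Z₂| ≤ 1.96): 9.1% at 0.5 and 8.4% at 0.68.

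**Step 3: simulation with t tests, 18 per arm** (20,000 null trials per setting, equal and autoregressive correlation; the EA-CCR row from 60,000 trials per setting, *r* = 0.3 to 0.8).

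| What may count as success | Chance of a false positive |
|---|---|
| One t test at one visit | 4.8-5.2% |
| t test at either visit | 8.4-9.3% |
| Either visit, or ANOVA group-by-time | 9.0-10.2% |
| Either visit, in favour of EA-CCR only | 4.3-4.6% (nominal 2.5%) |

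The first row confirms that the simulation is calibrated. Moving from one visit to two accounts for most of the inflation; the group-by-time test adds about one percentage point or less.

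**Step 4: after repair.** One named contrast tested once has 5% error. If either week may establish success, 0.025 + 0.025 = 0.05 bounds the error at 5% whatever the correlation.

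**The case against.** **The plan can be read without inflation.** If the two-sample tests were only follow-ups to a significant group-by-time test, the simulated error would be about 4-5%. That is a common practice, but the article states no such gate. It does not state that any test suffices either. This stands as a reason to make the 8-10% conditional. It does not supply the missing rule.

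**A statistical analysis plan that is not shown may settle it.** That is fair for the hierarchy of tests. It is weaker for the time point, which is part of the definition of the primary outcome.

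**It is a pilot.** With 36 participants, no power basis and an aim of preliminary evidence, no confirmatory claim depends on the result. This stands and lowers the severity. The article nevertheless states a superiority-type hypothesis and a significance threshold, so it needs to say which result answers the hypothesis.

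**Stronger readings that the article does not support.**
- A reader might put the error near 14%. That requires also counting an ANOVA group effect on raw scores averaged over baseline (13.5-14.7% in simulation), which is not a test of change. An ANOVA on the two change scores gives about 13% only if its group and group-by-time terms both count as well. That group-by-time term asks whether the effect differs between visits, not whether EA-CCR is superior.
- A reader might count the within-arm paired tests as routes to success. They cannot reject a null about EA-CCR against CCR.
- A reader might see the per-protocol and full analysis sets as a free choice. The article makes the first the efficacy analysis and calls the second supplementary.
- The choice between t and Wilcoxon tests is conventional and normally follows the distribution of the data.
- The article does not promise a 5% error rate for the primary as a whole; it sets a threshold per P value.

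**Conclusion.** The point holds in a limited form. Neither the ADAS-K-cog primary nor the null hypothesis names a time point, and between-group change is tested at two visits by two kinds of test at 0.05 each, with no statement of which result decides. If any of these results may count, the two-sided chance of a false positive is about 8-10%. In favour of EA-CCR at either visit it is about 4.5% against 2.5%. The size depends on that condition and on the assumed correlations. The lack of a defined conclusion for a mixed result depends on neither. Severity: should-fix, given the pilot aim.

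**What to change.** Before the data are analysed, name one primary between-group contrast. One example is the EA-CCR minus CCR difference in ADAS-K-cog at week 8 (end of intervention) from a single baseline-adjusted model (ANCOVA), tested once at two-sided 0.05 and reported with its 95% CI. The article ranks neither week above the other, so the choice of visit is the sponsor's. If either week may establish success, test each at 0.025. State the same time point in the Primary outcome and Hypothesis sections.

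Label the other visit, the other tests, the within-arm comparisons and the age subanalyses as secondary or supportive.

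The cost is protocol and analysis wording, with no added participants, visits or data. The sponsor gives up claiming the primary on an alternative visit or test or, under the 0.025 option, accepts a stricter threshold at each week.

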#### Secondary outcomes

The secondary outcomes will include changes in the MoCA-K scale, CES-D, K-ADL scale, K-IADL scale, and EQ-5D-5 L scores over time.

The MoCA scale, which was developed by Nasreddine et al., is a clinician-friendly, validated, brief instrument with high sensitivity and specificity for the detection of MCI [30]. It has been translated into Korean and validated [31].

The CES-D is a widely used 20-item self-report instrument designed to measure depressed affect, positive affect, somatic and retarded activity, and interpersonal relationships. Patients are asked to rate each item using an ordinal 4-point Likert scale [32].

The K-ADL and K-IADL scales will be used to assess physical function. The K-ADL scale was developed to assess basic activities of the elderly, including dressing, washing, bathing/showering, eating, getting out of bed/room, using the toilet, and controlling urination. The K-IADL scale is used to estimate more complex activities necessary for independent daily life. These include personal grooming, household chores, preparing meals, doing laundry, going out within a short distance, using transportation, shopping, managing money, making phone calls, and taking medications [33]. A combination of ADL and IADL items in a single scale would provide an enhanced measurement range and sensitivity [34].

The European Quality of Life Five Dimension Scale (EQ-5D) is a generic instrument for assessment of the health-related quality of life. It is based on a descriptive system that defines health in terms of five dimensions: mobility, self-care, usual activities, pain/discomfort, and anxiety/depression. Each dimension has three response categories: no, some, or extreme problems. The EQ-5D-5 L, which will be used in this study, is a new version of the EQ-5D that includes five levels of severity in each of the existing five dimensions [35].

### Incidence of adverse events

Adverse events (AEs) are undesirable and unintentional signs, symptoms, or diseases that appear during or after treatment in a clinical trial. The participants in this study will be required to voluntarily report any AEs. All AEs that occur during the trial will be documented. Possible AEs include skin irritation; bleeding; local hematoma; pallor, sweating or dizziness; fainting during EA treatment; needle retention after treatment; continuous severe pain for > 1 h after EA; objective worsening of existing symptoms; and undesirable and unintentional signs, symptoms, or diseases. The CRC will record all AEs in detail, including the time and date of occurrence, degree of severity, any measures related to treatment of the AE, and any potentially causal relationship between the treatment and the AE, and will report all AEs to the PI and relevant IRB. In case of SAEs, defined as those causing severe disability or malfunction, appropriate measures will be taken, and the incident will be immediately reported to the PI and relevant IRB. In case an AE occurs because of the clinical trial, participants will notify the CRC and PI and will be compensated.

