**Discussion:**

The study is expected to provide preliminary evidence regarding the efficacy, safety, and usefulness of EA-CCR for the treatment of MCI.

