### Participant recruitment

Participants will be recruited at DongShin University Gwangju Korean Medicine Hospital, Republic of Korea. The study will be advertised through local newspapers, the Internet, and posters in communities and hospitals. Individuals can enquire about participation through the telephone or personal visits. When interested individuals visit the clinical research center at DongShin University Gwangju Korean Medicine Hospital, they will receive an explanation about the study from the clinical research coordinator (CRC) and will be requested to voluntarily sign an informed consent form before participation. All recruited individuals will be screened by the Korean version of the Mini-Mental State Examination (K-MMSE) and MoCA-K for confirmation that all inclusion criteria are met. The CRC will continuously monitor the medical condition of the enrolled participants to ensure adherence to the intervention protocols.

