### Inclusion criteria

Participants meeting all of the following criteria will be included in the study: (1) age 55 to 85 years; (2) fulfillment of the Petersen diagnostic criteria for MCI [1, 2] with memory impairment for at least 3 months, (3) K-MMSE score of 20–23, (4) MoCA-K scale score of 0–22, (5) Korean language fluency that is adequate for reliable completion of all study assessments, and (6) voluntary provision of informed consent.

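### Voluntary reporting by memory-impaired, unblinded participants is the only stated route to adverse events, which risks under-counting them; prompted enquiry at existing contacts would be a cheap improvement

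*Protocol article*

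**What the plan says.** The section Incidence of adverse events gives the route by which events are found: "The participants in this study will be required to voluntarily report any AEs". Its closing sentence, on events caused by the trial, likewise has the participant inform the clinical research coordinator (CRC) and the principal investigator. The same section promises that "All AEs that occur during the trial will be documented" and that "The CRC will record all AEs in detail, including the time and date of occurrence". It then lists possible events. Several are tied to electroacupuncture (EA), such as fainting during EA, a needle left in place, or prolonged pain afterwards; others are general.

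Three other places bear on the point:

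- Inclusion criteria: entry requires "fulfillment of the Petersen diagnostic criteria for MCI [1, 2] with memory impairment for at least 3 months".
- Abstract, Discussion: "The study is expected to provide preliminary evidence regarding the efficacy, safety, and usefulness of EA-CCR for the treatment of MCI". The Background and the main Discussion also name safety.
- Participant recruitment: "The CRC will continuously monitor the medical condition of the enrolled participants to ensure adherence to the intervention protocols".

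Both arms are scheduled for 24 sessions over 8 weeks (Interventions; RehaCom cognitive rehabilitation). After that, the only assessment stated is 12 weeks later, at week 20. The Discussion acknowledges that acupuncturists and participants are not blinded.

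**The concern.** Spontaneous reporting asks the participant to notice an event, remember it and decide to mention it. In this trial memory impairment is a condition of entry, so the method leans on the faculty that the disease affects. The promise to document all events and the CRC's detailed recording describe what happens once an event is known; they do not say how an unreported one comes to light.

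Two kinds of event are most exposed: those that arise at home between sessions, and those in the 12 weeks after treatment. Capture could also differ by arm. Participants know their allocation, contact time differs, and some listed events are specific to needling.

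What is at stake is the safety statement. With 18 participants per arm, a few missed events can turn a small count into none, and a pilot's event counts are carried into the planning of later trials.

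**Working it through.** **Inputs from the protocol article**
- Sessions: 3 per week × 8 weeks = 24 in each arm. This reproduces the stated 24.
- Session length: 30 min for computer-based cognitive rehabilitation (CCR) alone; 30 + 30 = 60 min for EA-CCR (Interventions).
- Assessments: baseline, week 8 and week 20. The stretch after treatment with no stated contact is 20 − 8 = 12 weeks.
- Arm size: 18 (Sample size estimation), with no power calculation.
- Event rate and probability that an event is reported: not given. All values for these below are assumptions.

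**1. Chance of recording no event in one arm**

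This applies only to events not observed at a session. Let p be the true incidence per participant, c the probability that an affected participant's event is recorded, and n = 18, with participants independent. Then P(none recorded) = (1 − p·c)^n and the expected recorded count is n·p·c. With p = 20%:

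| Capture c | p·c | P(none) | Expected count |
|---|---|---|---|
| 100% | 0.20 | 0.80^18 = 1.8% | 3.6 |
| 75% | 0.15 | 0.85^18 = 5.4% | 2.7 |
| 50% | 0.10 | 0.90^18 = 15% | 1.8 |

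**2. What a count of 0/18 would rule out**

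The one-sided 95% upper bound on the recorded rate is 1 − 0.05^(1/18) = 15.3%. Dividing by c gives the bound on the true rate: 15.3% at full capture, 19.2% at 80% and 30.7% at 50%.

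**3. Comparison between arms**

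Suppose both arms have the same true risk p. The spurious difference is p × (c in EA-CCR − c in CCR).
- p = 30%, capture 80% in EA-CCR and 50% in CCR: 18 × 0.30 × 0.80 = 4.3 against 18 × 0.30 × 0.50 = 2.7, a difference of +9 percentage points.
- Capture rates reversed: 2.7 against 4.3, or −9 points.
- p from 10% to 40% with the same pair of capture rates: 3 to 12 points, in either direction.
- Equal capture of 50%: both counts halve and the difference is zero.

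The sign therefore depends wholly on which arm has the better capture, and the documents do not settle that.

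**The case against.** The strongest reply is that the article does not say voluntary reports are the sole source. It commits to documenting all events and has the CRC follow participants' medical condition. It is also a condensed account: the schedule figure is not shown, and the CRFs and operating procedures, where visit prompts often sit, are not at hand. Mild cognitive impairment is described as slight, dementia is excluded, and a self-report depression scale is used.

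Much of this softens the point without answering it. The article does not leave the method open: it names one, and the participant initiates it. The CRC's monitoring is stated to serve adherence. The unseen forms may contain prompts, but the text as written does not rely on them.

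Some stronger readings are tempting and are not supported:

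- *That doctors see events only in the EA-CCR arm, so every CCR-arm event rests on unaided recall.* Interventions has Korean medicine doctors administering the treatment after describing both arms, and both arms attend 24 sessions. Events during a CCR session can be seen too, and during treatment the recall interval is days.
- *That events will certainly be under-counted, and unequally.* No figure in the documents establishes either. Better capture in EA-CCR would make that arm look worse, poorer capture would make it look better, and equal capture would leave no spurious difference where true risks are equal.
- *That the chances of recording none apply to all EA events.* Needling events seen by the doctor do not depend on being volunteered, so those figures hold only for unobserved events.

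**Conclusion.** The point holds as a risk. The only stated route to AEs, beyond incidental observation at sessions, is spontaneous reporting by people selected for memory impairment and aware of their allocation. Under-counting is plausible, chiefly between sessions and after week 8, and unequal capture is possible. Neither its size nor its direction can be derived from the documents.

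The illustration, a rise in the chance of recording none from 1.8% to between 5.4% and 15%, rests on an assumed 20% incidence of unobserved events and assumed capture of 75% to 50%. It shows how sensitive a safety statement from 18 participants is to missed events; it is not an estimate for this trial. This is a cheap improvement to data collection and does not invalidate the trial.

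**What to change.** Replace voluntary reporting as the stated method with prompted enquiry, identical in both arms: one open question and a short fixed checklist at each treatment session and at the week-8 and week-20 assessments. Include a guardian where one is present. Keep spontaneous reports as an additional source, and tabulate prompted and volunteered events separately by arm.

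No new visits are needed. The costs are a small CRF change, more minor events recorded, and approval of the amendment by the Ministry of Food and Drug Safety and the institutional review board, as Quality assurance requires. Recruitment began in November 2018, so a change made mid-trial would mix two methods among 36 participants. In that case, flag which participants were followed under each method and report the event counts accordingly. If the full protocol or CRFs already prescribe such questions, it is enough to say so in the AE section.
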